### Statistical considerations

#### Sample size and accrual

Based on retrospective data, the prevalence of metastatic SNs is expected to be 30%. Our gold standard is the histological outcome of SNB (absence or presence and size of metastases in the SN). Submicrometastases (i.e. <0.1 mm at any site or 0.4 mm subcapsular) in melanoma patients, and isolated tumor cells (i.e. ≤0.2 mm) in breast cancer patients will be considered negative: a negative FNAC is accepted in these cases. Based on previous reports, we expect to find around 10% of these submicrometastases and isolated tumor cells in both melanoma and breast cancer patients [52, 53]. Considering this, the maximum achievable sensitivity of FNAC will be 90%. For this sensitivity, and a 95% confidence interval of 80–100% (With a two-sided significance level α = 0.05 and power 1 – β = 0.8), the required sample size is 116 considering a 30% prevalence of metastatic SNs. Around 3% of patients are expected to have a negative lymphoscintigram: the sample size will be increased to 120 patients.

With an average accrual rate of 60 patients per year, maximum accrual will be met at 2 years post start of study.

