## Abstract

**Background:**

Sentinel node (SN) biopsy (SNB) detects clinically occult metastases of breast cancer and melanoma in 20–30%. Wound infections, seroma and lymph edema occur in up to 10%. Targeted ultrasound (US) of the SN, (with fine needle aspiration cytology (FNAC) if appropriate) has been investigated as a minimally invasive alternative, but reported sensitivity rates are too low to replace SNB. Our hypothesis is that the use of a handheld gamma probe concomitant with US may improve sensitivity.

Our aim is to provide an overview of the current literature on preoperative nodal staging of clinical N0 melanoma patients, report on a pilot, and present a study protocol for a minimally invasive alternative to the SNB: **G**amma probe and **Ul**trasound guided **F**ine needle aspiration cytology of the sentinel node (GULF trial).

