#### Hypotheses GULF trial

We hypothesize that a sensitivity of 90% with a 95% confidence interval of 80% - 100% is achievable. Secondly, we expect that a SN identification rate of more than 75% is feasible.

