### Pilot

Our pilot results show that correct identification of the SN for FNAC was possible in 90%, and that the sampled material was representative in 95% of FNAC samples. CNB was representative in only 60%. This confirms that the described technique for targeted US-FNAC of the SN is feasible. CNB will not be added to the study procedure considering the low rate of representative tissue in the pilot phase.

If an acceptable sensitivity can be achieved for FNAC, patients can proceed to undergo radical lymph node dissection immediately in case of positive FNAC, bypassing the SNB procedure. When the FNAC sample is negative, surgeons can choose to perform a SNB or continue with only surgical excision of the primary tumor and monitoring of potential lymph node involvement at follow up visits. This way up to 80% of patients eligible for SNB can be spared this invasive procedure and the risk of morbidity related to this procedure. Furthermore, for melanoma patients this would mean that general anesthesia is no longer needed, as WLE can be performed under local anesthesia. Ultimately operative nodal staging may become completely obsolete.

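### Small deposits are classed as reference-negative, yet their 10% share is used to cap sensitivity at 90%; on the reading that yields the cap, 116 patients give about 31 positives, not 35

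*Protocol article*

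**What the plan says.** All the relevant statements but one stand in the section Sample size and accrual of the protocol article.

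- Prevalence: "Based on retrospective data, the prevalence of metastatic SNs is expected to be 30" per cent. No size cut-off is attached to this figure.
- Reference standard: SNB histology, including the size of any metastasis. Deposits below the stated cut-offs (submicrometastases in melanoma, isolated tumour cells in breast cancer) "will be considered negative: a negative FNAC is accepted in these cases".
- Their frequency: "we expect to find around 10% of these submicrometastases and isolated tumor cells in both melanoma and breast cancer patients". The denominator of this 10% is not given.
- The inference drawn from it: "Considering this, the maximum achievable sensitivity of FNAC will be 90" per cent.
- The sample size: 116 patients for a sensitivity of 90% with a 95% confidence interval of 80–100% at 30% prevalence, raised to 120 for about 3% negative lymphoscintigrams.

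The section Hypotheses GULF trial gives the same 90% separately, as an expectation and not as a ceiling: "We hypothesize that a sensitivity of 90% with a 95% confidence interval of 80% - 100% is achievable".

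**The concern.** Sensitivity is the share of reference-positive patients whom the index test detects. A patient who is reference-negative cannot be a false negative. If the small deposits are negative, missing them costs no sensitivity, and they cannot be the reason why sensitivity stops at 90%. If they are the reason, they must be in the denominator as positives. The article asserts both within a few sentences.

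Two things depend on the answer. The first is the expected number of reference-positives, which alone determines the precision of the primary estimate. The second is the estimate itself, since the same FNAC results give a different sensitivity according to whether the small deposits are counted.

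**Working it through.** **Inputs** (all from Sample size and accrual): sensitivity 0.90, half-width 0.10, two-sided α 0.05, prevalence 0.30, share of small deposits about 0.10, negative lymphoscintigram 0.03.

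**1. The plan's own figure.** The Wald precision formula for one proportion gives

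- positives = 1.96² × 0.90 × 0.10 / 0.10² = 34.57, that is 35;
- N = 34.57 / 0.30 = 115.2, so 116;
- 116 / 0.97 = 119.6, so 120.

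Both stated figures reproduce. The arithmetic is sound, and the question is about its inputs. The stated power of 0.8 does not enter this formula.

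**2. The ceiling.** Take 100 patients, 30 with any SN deposit. A 10% share of those 30 is 3 patients with small deposits only, leaving 27 with larger ones. Suppose FNAC finds every larger deposit and no small one.

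- Small deposits negative, as the rule says: 27/27 = 100%.
- Small deposits positive: 27/30 = 90%.

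Only the second line gives the stated maximum, and it contradicts the stated rule.

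**3. What the 10% refers to.** If it meant 10% of all patients, 10 of the 30 positives would be small deposits and the cap would be 20/30 = 67%. The 90% cap therefore requires 10% of SN-positive patients, and it requires that the 30% includes the small deposits.

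**4. Expected positives under the stated rule, on that reading.**

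- Usable prevalence: 0.30 × 0.90 = 0.27.
- Positives among 116: 116 × 0.27 = 31.3, against 116 × 0.30 = 34.8.
- Wald half-width at 0.90: 1.96 × √(0.09 / 31.32) = 0.105, against 1.96 × √(0.09 / 34.8) = 0.100.
- Exact (Clopper–Pearson) 95% CI for 28/31: about 74–98%.
- N that would restore a half-width of 10 points: 34.57 / 0.27 = 128.05, so 129 (130 if positives are first rounded up to 35). After division by 0.97 this is 133 to 135.

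**5. If the 30% already excludes small deposits.** Step 1 stands unchanged, with N = 116 and about 35 positives. The 90% ceiling still has no basis.

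**6. Effect on the estimate.** Illustration in expected counts: 35 patients with any deposit, 3.5 of them small, so 31.5 larger. FNAC detects 90% of the larger ones (0.90 × 31.5 = 28.35) and none of the small ones.

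- Small deposits negative: 28.35 / 31.5 = 90%.
- Small deposits positive: 28.35 / 35 = 81%.

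**The case against.** The strongest reply is that the rule itself is clear and only its justification is faulty. The reference standard is SNB histology with size, the small deposits are declared negative without condition, and the ceiling belongs to the sample-size rationale, not to an analysis rule. The value of 90% survives as a hypothesis stated elsewhere, and 116 and 120 follow from the stated inputs. It is also nowhere stated that the 30% includes the small deposits; it rests on retrospective data that the article does not show. All of this stands. It limits the size of the problem but does not reconcile the two sentences.

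A reader might infer more than the article supports:

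- *That the number of positives is certainly wrong.* Inclusion of the small deposits in the 30% follows from the cap but is not stated.
- *That the choice of rule decides whether the result lies above or below 80%.* In the illustration both estimates, 90% and 81%, are above 80%. Moreover, 80% is the lower end of the anticipated interval and is not given as a pass mark.
- *That reference status depends on the FNAC result.* The clause about accepting a negative FNAC describes a consequence of a rule that is already unconditional.
- *That positives could fall to about 23 or 21.* The 23 needs the 10% to refer to all patients, which does not give a 90% cap. The 21 applies the 10% deduction to the bottom of the 20–30% range in the Abstract, which the plan does not use.
- *That the 30% conflicts with the rest of the article.* It lies within the range in the Abstract ("detects clinically occult metastases of breast cancer and melanoma in 20–30" per cent). The remark in the Discussion that up to 80% could be spared SNB is an upper bound. Neither is a contradiction.

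**Conclusion.** The contradiction is real and no reading removes it: deposits classed as negative cannot limit sensitivity to 90%. The consequence for precision is modest and conditional. If the 30% includes the small deposits, as the cap implies, the trial should expect about 31 positives among 116 rather than 35, and a Wald half-width of about 10.5 points, so the 10-point target is narrowly missed. If the 30% excludes them, the sample size stands and only the ceiling is wrong.

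The consequence for the primary estimate is larger, 9 points in the illustration. It arises only if the analysis follows the logic of the cap instead of the stated rule, and it assumes a 10% share of small deposits, all missed by FNAC.

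**What to change.** 1. Keep one reference rule based on SNB deposit size alone: patients whose only deposits are below the stated cut-offs are reference-negative whatever FNAC shows.
2. Delete the derivation of a maximum achievable sensitivity, and present 90% as the planning hypothesis already given under Hypotheses GULF trial.
3. State whether the 30% prevalence is before or after the size cut-off. If before, restate the expected positives as about 31 of 116 and give the resulting interval width (Wald half-width about 10.5 points; exact 95% CI for 28/31 about 74–98%).

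The cost is a few sentences of wording. The one downside is that, if the 30% is before the cut-off, the stated precision becomes slightly less favourable.

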#### Cytology or histology?

In order to reach the sample size needed for proof of concept with accurate power and within an acceptable term, both melanoma patients and breast cancer patients will be included in the GULF trial. The SN procedure is uniformly applied for both melanoma and breast cancer, and breast cancer patients may equally benefit from a minimally invasive alternative for the SN. All patients will undergo FNAC. Since metastatic size may have clinical implications for breast cancer patients [18], a subset of 10 breast cancer patients will undergo CNB additionally after FNAC. This allows for a comparison of results between CNB, FNAC and SNB.

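### The 116 patients come from a Wald precision formula alone; the stated 80% power has no null sensitivity and plays no part in the figure

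*Protocol article*

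**What the plan says.** The primary endpoint is the sensitivity of gamma-probe and ultrasound guided needle sampling, judged against the histology of the surgically removed sentinel node. The section on the trial's hypotheses states: "We hypothesize that a sensitivity of 90% with a 95% confidence interval of 80% - 100% is achievable".

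Sample size and accrual builds the number of patients as follows:

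- Sensitivity, in per cent: "Considering this, the maximum achievable sensitivity of FNAC will be 90".
- Interval, in per cent: "For this sensitivity, and a 95% confidence interval of 80–100".
- Prevalence, in per cent: "the prevalence of metastatic SNs is expected to be 30".
- Error rates and result: "With a two-sided significance level α = 0.05 and power 1 – β = 0.8), the required sample size is 116".
- Inflation: "Around 3% of patients are expected to have a negative lymphoscintigram: the sample size will be increased to 120 patients".

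No null or minimum acceptable sensitivity appears in that section, in the hypotheses, in the study aims or among the endpoints. The 75% that the endpoints section calls acceptable applies to the sentinel node identification rate, not to sensitivity.

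**The concern.** A confidence interval width and a power are different design targets. Width needs an expected proportion and a half-width. Power also needs a null value, and a β that enters the formula. The sentence presents 116 as meeting both targets at once, but supplies inputs only for the first.

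This matters because it is the only justification given for the size of the trial, on its primary endpoint. The Discussion links an acceptable sensitivity to consequences for patients: dissection without a prior sentinel node biopsy after positive cytology, and possible omission of the biopsy after negative cytology. A reader who sees a power of 0.8 will think the trial is likely to separate 90% from some clearly lower sensitivity. A reader who sees 80–100% will expect a lower limit at 80% if 90% is observed. Both expectations need checking.

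**Working it through.** **Inputs from the document.** Expected sensitivity 0.90; half-width 0.10 (from 80–100%); prevalence 0.30; two-sided α 0.05; power 0.80; 3% negative lymphoscintigrams. **Assumption.** The null sensitivity is not stated. 0.80, the lower limit of the target interval, is used first, and other values follow.

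**1. Reproducing 116 and 120.** Wald half-width formula:

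- positives = 1.96² × 0.9 × 0.1 / 0.10² = 34.57
- patients = 34.57 / 0.30 = 115.2, rounded up to 116
- inflated = 116 / 0.97 = 119.6, rounded up to 120

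Both published figures are matched, and β appears nowhere.

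**2. Does any formula with 80% power give 116?** For 0.90 against 0.80:

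| Method | Positives | Patients at 30% |
|---|---|---|
| (z_α + z_β)² × 0.09 / 0.01, one-sided | 55.6 | about 185 |
| same, two-sided | 70.6 | about 235 |
| arcsine, one-sided | 76.8 | about 256 |
| arcsine, two-sided | 97.5 | about 325 |
| one-sample normal test, one-sided | 83 | 277 |
| one-sample normal test, two-sided | 108 | 360 |
| exact binomial, two-sided | 107–113 | 357–377 |

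The two-sided normal test is (1.96 × √0.16 + 0.842 × √0.09)² / 0.01 = 107.4, so 108. Exact power first passes 80% at 107 positives and stays above it from 113. None of these variants gives 116.

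**3. Power with the planned size, assumed null 80%, true sensitivity 90%.**

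- 35 positives, exact (Clopper-Pearson) or Wilson limits: the lower limit reaches 80% from 33/35; P(X ≥ 33) = 30.6%.
- Averaged over a binomial number of positives: at 116 patients, 24.8% (exact) or 27.5% (Wilson); at 120 patients, 26.0% or 28.8%.
- 35 positives, Wald limit: reached from 32/35, probability 53.1%. That rule has a one-sided type I error of 6.1% instead of 2.5%.

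**4. Other assumed nulls** (35 positives, exact test, upper-tail error at most 2.5%):

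| Null | Positives needed | Power at 90% |
|---|---|---|
| 80% | 33/35 | 31% |
| 75% | 32/35 | 53% |
| 70% | 31/35 | 73% |
| 69% | 30/35 | 87% |

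Power of 80% is reached only for a null of about 69% or lower.

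**5. The interval.** Wald at exactly 90% with 35 positives is 0.90 ± 1.96 × √(0.09/35) = 80.1–99.9%, the stated interval. Its true coverage at a sensitivity of 90% is 87%, not 95%. Exactly 90% cannot occur with 35 positives; the nearest results give:

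| Result | Exact | Wilson | Wald |
|---|---|---|---|
| 31/35 (88.6%) | 73.3–96.8% | 74.0–95.5% | 78.0–99.1% |
| 32/35 (91.4%) | 76.9–98.2% | 77.6–97.0% | 82.2–100.7% |

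At an observed 90%, an exact lower limit of 80% is not reached with 54/60 (79.5%) and is reached with 63/70 (80.5%). Interpolation puts the crossing at 65 positives, so about 65–70 are needed, or 217–234 patients.

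**The case against.** Sizing a single-arm accuracy study by precision is legitimate, and the Wald formula is a conventional planning tool. The 80–100% interval is what that formula gives at 90% with about 35 positives, so it is not an arithmetic error. That stands. What remains is that the interval is optimistic: exact and Wilson lower limits near 90% fall about 2 to 7 points below 80%.

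The document never makes 80% a null or a success threshold. That also stands, and it limits three stronger readings that a reader might infer:

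- That the trial's real power is simply 25–31%. This holds only for an assumed null of 80% with exact or Wilson limits; other nulls give 53%, 73% or more.
- That the trial will fail to exclude an unacceptable sensitivity. The document does not say what sensitivity is unacceptable, nor that the lower limit must reach 80%.
- That about 360 patients are required. That follows only if the sponsor wants 80% power against 80%.

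The remark on power under the heading Cytology or histology? ("In order to reach the sample size needed for proof of concept with accurate power") is a general reason for enrolling both tumour types. It is not a second calculation and adds nothing to the point.

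Finally, the interval method for the analysis may well be set in a full protocol or analysis plan that is not shown. Its absence from the article is no fault. None of this supports the power statement, which is in the text and is not met by the calculation given.

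**Conclusion.** The point holds as a wrong statement in the sample-size justification. That 116 and 120 are precision figures is established by exact reproduction and needs no assumption. So is the absence of β and of a null sensitivity. The 80% power is therefore unsupported.

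The size of the shortfall is conditional. Against an assumed null of 80%, power at a true 90% is about 31% with 35 positives and exact or Wilson limits, about 25–29% averaged over the random number of positives, and about 53% with the Wald limit. The claimed 80% would be true only against a null of about 69% or lower, a sensitivity bound that the plan does not set. These figures also rest on the plan's own 90% sensitivity and 30% prevalence. The expected interval should read roughly 73–98%, from the exact lower limit at 31/35 to the exact upper limit at 32/35.

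**What to change.** In Sample size and accrual, delete the clause on α and power and say that the size rests on the precision of the sensitivity estimate. There and in the hypotheses section, replace 80–100% with the interval expected from about 35 positives under exact or Wilson limits, roughly 73–98%, and name the method. Use the same method for the primary sensitivity estimate, so that the planned and reported intervals agree.

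If a power statement is to be kept, state the null sensitivity and report the power actually achieved against it with about 35 positives.

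The cost is a few sentences and less favourable planning figures. No extra patients and no change in study procedures are requested.

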### Statistical analysis plan

The main analysis addressing the primary endpoint will be performed after inclusion of all 120 patients. No interim analysis is planned for this endpoint.

### Ethical considerations

This study has been approved by the Erasmus MC medical-ethical committee. The study will be conducted according to the principles of the Declaration of Helsinki and in accordance with national and regional legislation, guidelines, regulations and acts.

## Discussion

Currently SNB is the most important staging procedure for clinically N0 melanoma patients, especially in the light of trial participation for adjuvant therapies based on N-status [20, 21, 54]. The therapeutic role of SNB for melanoma is still under debate [55–57]. Considering the fact that this is a surgical staging procedure associated with complications in up to 10% of patients, our group sought to investigate a more minimally invasive alternative.

The ongoing improvement of imaging techniques (i.e. more accurate and detailed US imaging) and increased experience with FNAC renders combined US-FNAC as a high potential minimally invasive alternative for surgical SNB [31, 32]. Correct transcutaneous identification of the SN forms the main obstacle for broad application of this technique as this is key in obtaining reliable FNAC.

The current study aims to give an overview of the current melanoma literature, report a pilot and present a study protocol for a minimally invasive technique to investigate the SN using gamma probe guided US-FNAC.

### Overview of the literature

The studies presented provide evidence that it is difficult to detect clinically occult lymph node metastases in melanoma patients, and although some studies have achieved high sensitivity and specificity rates, these results have not been reproduced by other groups. There are many differences between the reported studies; namely retrospective vs. prospective study setting; US prior to lymphoscintigraphy vs. targeted US after lymphoscintigraphy; the number of persons performing US and their expertise; variation in US morphology criteria used to discriminate between benign and suspicious or malignant lymph nodes; and use of FNAC or not. Al these factors will have contributed to the outcome of these studies. It is interesting to see that sensitivity rates are low in the studies that performed an US of the entire lymph node basin without knowing the location of the SN (s), but that even in the studies were targeted US of the SN area was applied, sensitivity rates could be as low as 22% [58] and as high as 82% [31] or even a perfect 100% [36] as well. Thompson et al. proposed a possible explanation for these disparate results; many of the micrometastases present in SNs are too small to be detected by the US-equipment used [59, 60]. However, Voit et al. demonstrated that it was possible to successfully perform a FNAC in a lesion as small as 0.4 mm. Nevertheless, most smaller SN metastases will be overlooked by US and/or missed by FNAC. The question is if this has any clinical implications.

As long as US-imaging is limited by a detection limit, and alternative imaging techniques are tested in pilot settings, the need for a reliable, minimal invasive easy to perform and replicate method to assess SN status remains. Hence the presentation of the GULF trial study protocol here.

### Pilot

Our pilot results show that correct identification of the SN for FNAC was possible in 90%, and that the sampled material was representative in 95% of FNAC samples. CNB was representative in only 60%. This confirms that the described technique for targeted US-FNAC of the SN is feasible. CNB will not be added to the study procedure considering the low rate of representative tissue in the pilot phase.

If an acceptable sensitivity can be achieved for FNAC, patients can proceed to undergo radical lymph node dissection immediately in case of positive FNAC, bypassing the SNB procedure. When the FNAC sample is negative, surgeons can choose to perform a SNB or continue with only surgical excision of the primary tumor and monitoring of potential lymph node involvement at follow up visits. This way up to 80% of patients eligible for SNB can be spared this invasive procedure and the risk of morbidity related to this procedure. Furthermore, for melanoma patients this would mean that general anesthesia is no longer needed, as WLE can be performed under local anesthesia. Ultimately operative nodal staging may become completely obsolete.

